## Abstract

**Background:**

The present study protocol describes the evaluation of a comprehensive integrated care model implemented at two hospital sites at the University Hospital of North Norway (UNN). The PAtient Centred Team (PACT) model includes proactive, patient-centred interdisciplinary teams that aim to improve the continuum and quality of care of frail elderly patients and reduce health care costs. The main objectives of the evaluation are to analyse the effectiveness and cost effectiveness of using patient-centred teams as part of routine service provision for this patient group. The evaluation will analyse the effect on patient health and functional status, patient experiences and hospital utilisation, and it will conduct an economic evaluation. This paper describes the PACT model and the rationale for and design of the planned effectiveness and cost-effectiveness study.

**Methods/design:**

This is a prospective, non-randomised matched control before-and-after intervention study. Patients in the intervention group will be recruited from the hospital sites that have implemented the PACT model. The controls will be recruited from two hospitals without the model. The control patients and the index patients will be matched according to sex, age and number of long-term conditions. The study aims to include 600 patients in each group, which will provide sufficient power to detect a clinical change in the primary outcome. The primary outcome is the physical dimension of the Short Form Health Survey (SF-36). Secondary outcomes are the Patient Generated Index (PGI), the Patient Activation Measure (PAM), the Patient Assessment of Chronic Illness Care (PACIC), hospitalisation and length of stay. The cost-effectiveness study takes a health provider perspective and calculates the cost per quality-adjusted life-years (QALYs) gained. The data will be collected at baseline, 6 and 12 months. The data will be analysed using techniques and models that recognise the lack of randomisation and the correlation of cost and effect data.

**Discussion:**

The study results will provide knowledge about whether the integrated care model implemented at UNN improves the quality of care for the frail elderly with multiple conditions. The study will establish whether the PAC. T model improves health and functional status and is cost effective compared to the usual care for this patient group.

**Trial registration:**

ClinicalTrials.gov: NCT02541474

## Background

As the population ages, the proportion of older persons admitted to hospital is continuously increasing. Older people are found to have higher admission rates and longer hospital stays than the general population [1]. Patients aged 67 years and older account for 35 % of the hospital admissions in Norway [2]. This is comparable to other countries. Persons aged 65 and over account for approximately 38 % of the hospital admissions in the United Kingdom [1] and 36 % in the United States [3]. Older people are also major consumers of hospital-based acute services [4]. The current disease-oriented and episodic models of care do not adequately respond to the complex care needs of older patients [5] and patients with multimorbidity [6]. Compared with younger persons, older adults have longer stays, their visits have a greater level of urgency, they are more likely to be readmitted, and they experience higher rates of adverse health outcomes after discharge [5]. Studies show that there is a considerable risk of adverse events in relation to the transition of patients between hospitals and primary care services and that information exchange at discharge is often insufficient [7, 8]. Thus, there is a growing need for better care coordination between and within primary and specialist health care services to ensure patient safety and continuity of care [9].

The efficient and effective management of acutely ill, complex inpatients poses one of the greatest challenges in current hospital care [10]. Health care utilisation and costs increase significantly with increasing number of chronic conditions [11]. One way to improve the management of the older patients with multimorbidity is to use patient-centred interdisciplinary teams. Interdisciplinary team work offers an integrated approach to providing coordinated health care to “high-risk” patients with complex long-term needs. Team work has been considered good practice for more than two decades [12]. However, little evidence exists that these types of interventions are effective. Five recent systematic reviews found mixed results and they reported that there exists no clear evidence that these interventions are effective or cost effective [4, 13–16]. These reviews reported that some well-integrated models have improved the process of care and have the potential to reduce hospitalisation and nursing-home use [13]. Some of the studies also reported improved prescribing and medication adherence [14]. One of the reviews that specifically looked into the cost effectiveness of multidisciplinary teams found the same trend of insufficient evidence. This review reported mixed results and a high degree of heterogeneity and low-quality evaluations [15]. All these reviews concluded that more research is needed in this area. They also argued that comparison among studies is difficult because of the heterogeneity in both how interdisciplinary teams work and the study populations analysed. This hampers the ability to develop best-practice models.

In our local setting, a recent report documented that two of the main challenges are the lack of attention to the personal context of the patients and the fragmented care delivery [17]. The need for a re-design of care delivery with more service integration and improved follow-up regimen seems particularly urgent for frail elderly patients with complex and long-term needs [18–20]. A large-scale project that facilitates more integrated and coordinated care for frail elderly medical patients is now under development at the University Hospital of North Norway (UNN). The Patient-Centred Team (PACT) model is being established at UNN Tromsø, UNN Harstad and their hosting municipalities. The purpose of the PACT model is to improve the continuum and quality of care for frail elderly patients and to reduce health care costs. The PACT model has been initiated and is solely driven by managers and clinical personnel at the hospital and at the community services.

The PACT model is inspired by the Chronic Care Model (CCM) and builds on two pillars. These are “the informed active patient” and “the pro-active prepared health care team”, engaging in “productive interactions” for “health and functional outcomes”. Both health management’s support and use of information and communication technology (ICT) are key supporting factors [21]. There is a growing evidence base for CCM’s effects on both care processes, health outcomes [22, 23] and cost savings [24]. CCM continues to inspire care reforms internationally [25, 26]. The Norwegian health authorities are pushing for a large system transformation towards a truly person-oriented integrated care model which broadly aligns with CCM-principles [18].

The present paper describes the effectiveness- and cost-effectiveness evaluation of the PACT model. The main aim of the evaluation project is to determine whether the PACT model improves health and functional status and is cost effective compared to usual care. First, we describe the PACT model now being implemented as part of routine care at two hospitals in northern Norway and their hosting municipalities. Second, an overview of the design and methods used in the effectiveness study and the economic evaluation is provided, followed by a brief discussion. The evaluation project is funded by a research grant from the regional health authorities Helse Nord (Grant No. HST1242/3-15).

### The PACT model

The PACT model is a comprehensive integrated care model that aims to ensure safe discharge and prevent hospital admissions for frail elderly patients with multiple conditions. The patient-centred and proactive interdisciplinary teams, which include both the community services and hospital staff, are the key element of the model. The main task of the team is to follow patients through the system and help them receive appropriate and timely health care services when needed at the most appropriate location. The team will include the patients and their families in planning and facilitating service integration. The patients will be actively involved in defining goals, assessing needs and making care plans and follow-up protocols. Patient involvement and engagement in care has been shown to improve health and functional outcomes [27]. The team will identify and assess needs early, provide support during discharge and follow-up, facilitate coordination and integrated services across the levels of care and support, and care for the patients outside the hospital. This might ease the transition, reduce unplanned hospital admissions, reduce the need for community services and improve or avoid deterioration in patient health outcomes.

The PACT model includes five main tasks: to identify the patients with a special need for coordinated care; to identify patient goals and conduct need assessments; to facilitate individualised care plans and tailored follow-up protocols; and to initiate meetings regarding the coordination and integration of patient care across service providers. In particular, the team will assess the risk of fall and the need for special aid and review medication lists. The team will also ensure that general practitioners (GPs) are informed and included in the planning process. The patients will remain a team responsibility until the community service provider has established appropriate care or until the patients can manage at home without help.

The core team consists of the team leader (ICL) and two full-time coordinators: one from the hospital and one from the community service. The core team will be responsible for the day-to-day management of the teamwork and ensuring that the patients receive appropriate and timely support and services. The interdisciplinary team further consists of a senior medical doctor, geriatric nurses, district nurses, physiotherapists, occupational therapists and one pharmacologist.

The local implementation and structure of the PACT model will vary between the two experimental regions, even if the service model has a formal selection procedure and a common core of services. The structure and organisation of the service model will cover complex areas such as patient logistics (regulating the patient flow through the system; knowing when and how blockages occur and resolving them; using various instruments, such as case management; discharge protocols; capacity constraints; and home monitoring and support with various means). Information logistics, such as team communication and information exchange, will also vary. The general aim of the PACT model, however, will be the same: to ensure that the patients receive the right treatment and care at the right time and in the most suitable location.

#### Status

At the time of writing, all team members, including a part-time recording secretary, have been appointed at the hospital in Tromsø. The test and developing phase is well underway. The team is now actively promoting their existence and services by visiting GPs, district nurses, other community service providers and hospital wards and clinics. The first patients have been referred to the team as part of the test phase, but no patients have yet been enrolled in the trial. The team has been assigned office space at the hospital and has scheduled two daily meetings to plan activities and discuss patients. In between team meetings, the team is conducting home visits, attending coordination meetings, writing case reports and updating patient records. The second hospital has finished the planning phase and will be operational by fall 2015.

## Methods/design

### Objectives and research questions

The main objective of the evaluation is to analyse the effectiveness and cost effectiveness of establishing patient-centred interdisciplinary teams (the PACT model) as part of routine health care delivery for frail elderly patients with multiple conditions. The evaluation will analyse the effect of the PACT model on patient health and functional status, patient experiences and hospital utilisation, and we will conduct an economic evaluation. The research questions (RQs) include the following:

#### Effectiveness evaluation

Does the PACT model affect the health outcomes and functional status of the patients?Does the PACT model improve patient experiences and have an impact on the areas in life that the patients themselves consider important?Does the PACT model reduce unplanned hospital admissions and length of stay?

#### Cost-effectiveness evaluation

4.Does the PACT model represent cost-effective resource use from a health provider perspective in the short term (trial-based evaluation)?5.Is the PACT service model more cost effective for any specific subgroups of patients, defined by age, conditions (diagnoses), co-morbidities and other baseline factors?6.Is the PACT model cost effective in a 10-year perspective (model-based evaluation)?

### Design

This evaluation study is a prospective non-randomized, matched control, before-and-after study [28]. We will compare all hospitalised patients meeting the inclusion criteria with patients receiving usual care in a control setting. The PACT model is directed at the organisational level or geographic site, affecting all patients within the uptake area. Therefore, the intervention and controls are separated in different hospitals to avoid contamination. The chosen design improves comparability between the patient populations by matching them on factors known to be important for outcomes (age, sex and number of conditions), adjusting for baseline differences between the populations with a before-after design and adjusting for known confounders by the propensity score method [29, 30].

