### Participants

The intervention group participants will be recruited consecutively until we have reached the target of 600 patients. As soon as the patients have signed the consent form, the intervention will start and the baseline data collection will begin. The follow-up period will be one year from the initial assessment for each patient.Inclusion criteria: Patients with emergency admission to the UNN internal medicine department in Tromsø and Harstad who are over the age of 65 years, have two or more long-term conditions and provide valid written informed consent (either by the patient or the next of kin).Exclusion criteria: Language barriers, life expectancy of less than three months and unable to provide written informed consent.

The control population will be recruited from the Nordland Hospital in Bodø and from the hospital UNN Narvik. When an index patient is identified in the hospitals using patient-centred teams, at least two eligible patients from the control hospitals will be identified. Sex, age and number of long-term conditions will be used to match the control patients to the index patients. The control patients will be subject to the same data collection as the intervention patients.

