#### Analyses

The analyses will use an intention-to-treat approach that includes all participants who signed the informed consent at the intervention and control hospitals. Missing data will be imputed using multiple imputations [48]. The multiple imputation model will include predictors from all time points, including health-related quality of life (SF-36), background variables, trial-related variables and resource use at baseline. Results with and without imputed data will be reported. The data will be analysed as a synthetic randomised controlled trial (RCT), using the propensity score method. This method postulates that each patient has a basic probability of the outcome of interest based on his/her characteristics [29]. Based on available knowledge for each patient (e.g. age, sex, education, ethnicity), we can calculate the patient’s propensity for the outcome (i.e. change in QoL). In subsequent analyses, we stratify analyses by this score. Within each stratum, the only known difference between patients with respect to the outcome will be the patient-centred teams. The fundamental requirement for validity in a causal analysis is that the variables used to create the propensity score are independent of the probability of getting the intervention. In common-sense terms, this means that in the synthetic study, within the same propensity score strata, the assignment to treatment is essentially the same as if it had been done by randomisation.

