### Ethics

The study has been granted ethical approval by the Regional Committees for Medical and Health Research Ethics in Norway (REK No. 2014/1707). We have been granted approval to use electronic hospital record (EHR) data to identify potential controls so that invitations to participate in the trial can be issued. We have also been granted approval to include patients unable to provide informed consent (due to cognitive impairment) as long as the next of kin provides informed consent on the patient’s behalf. All data will be temporarily stored on a secure research server at UNN. The local data protection supervisor has approved the study. The trial has been registered at ClinicalTrials.gov.

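### At the PACT hospitals one signature appears to cover both the service and the study, at the control hospitals only the study, so the intention-to-treat set may be selected differently in the two groups

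*Protocol article*

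**What the plan says.** All references are to the protocol article.

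- **Design** describes the comparison as "We will compare all hospitalised patients meeting the inclusion criteria with patients receiving usual care in a control setting" and gives the level of the intervention as "The PACT model is directed at the organisational level or geographic site, affecting all patients within the uptake area".
- **Participants** makes written consent, by the patient or next of kin, an inclusion criterion. For the intervention group it says: "As soon as the patients have signed the consent form, the intervention will start and the baseline data collection will begin". For controls it says: "The control patients will be subject to the same data collection as the intervention patients". Design says that controls receive usual care.
- **Ethics** explains how controls are found: hospital records are used "to identify potential controls so that invitations to participate in the trial can be issued".
- **Analyses** describes an "intention-to-treat approach that includes all participants who signed the informed consent at the intervention and control hospitals".
- **Status** reports that patients had already been referred to the team in a test phase, before anyone was enrolled in the trial.

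**The concern.** Intention-to-treat protects against what happens after entry to the analysis set. Here entry is the signature, and the signature stands for different things in the two groups. At a PACT hospital it is followed at once by the team and the questionnaires. At a control hospital it is followed by questionnaires alone.

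If patients at the PACT hospitals understand the form as covering both, some who would answer questionnaires but do not want the team will not sign, and they leave the PACT group before any analysis begins. The same kind of patient at a control hospital has no team to decline, signs, and is analysed. Nobody at a control hospital can be labelled as a would-be decliner, so this group cannot be removed from the controls either.

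The traits involved are plausibly related to outcome. The Patient experiences section itself links self-management to health and functioning, and makes self-management depend on motivation, knowledge and skills. A difference between the groups in such traits would be mixed with the PACT effect on change in SF-36, on activation and on hospital use. It would also weaken the claim under Analyses that, within propensity strata, assignment is essentially as if randomised.

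**Working it through.** **1. The passages side by side**

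| | PACT hospitals | Control hospitals |
|---|---|---|
| How patients enter | Consecutive recruitment, then consent | Found in records, matched, invited, then consent |
| What follows the signature | Intervention and baseline data collection | Data collection under usual care |
| Patient who would answer questionnaires but declines the team | May not sign, and is then not analysed | Signs and is analysed, but cannot be recognised |
| Analysis set | Those who signed | Those who signed |

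The last row is the same in both columns; the rows above it are not.

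**2. The plan's own figure**

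Sample size section: difference 4 points, SD 25, significance level 0.05, power 0.80, 600 per group.

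- n per group = 2 × 25² × (1.960 + 0.842)² / 4² ≈ 614, within 3% of 600.
- Standard error of the difference = 25 × √(2/600) = 1.443 points.
- Power with 600 per group = Φ(4/1.443 − 1.960) = 0.791.

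The stated figure is reproduced with a two-sided test and is not in dispute. The standard error is used below only as a yardstick.

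**3. What differential selection would do**

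Let q be the share of eligible patients in a group lost through not consenting, and d the mean change in those who consent minus that in those who do not. The mean among consenters exceeds the mean among all eligible patients by q × d. The bias in the group comparison is therefore

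bias = q(PACT) × d(PACT) − q(control) × d(control).

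The documents give none of these four quantities. Neither the sign nor the size of the bias can be computed from them.

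**4. Illustration with assumed inputs**

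Take only the loss due to declining the team, and assume that control consent is unrelated to the trait, so that the second term is zero. Then bias = q × d. The false-positive rate with no true effect is P(|Z + bias/1.443| > 1.960). If the bias runs against PACT, power for 4 points is Φ((4 − bias)/1.443 − 1.960).

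| Assumed q | Assumed d (points) | Bias (points) | Share of 4-point target | False-positive rate | Power if bias is against PACT |
|---|---|---|---|---|---|
| 10% | 5 | 0.5 | 0.125 | 0.064 | 0.679 |
| 20% | 5 | 1.0 | 0.25 | 0.107 | 0.547 |
| 30% | 5 | 1.5 | 0.375 | 0.180 | 0.410 |
| 20% | 10 | 2.0 | 0.50 | 0.283 | 0.283 |

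A wider grid (q from 10% to 40%, d from 3 to 8 points) gives a bias from 0.10 × 3 = 0.3 to 0.40 × 8 = 3.2 points.

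**5. How much the zero-control assumption matters**

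Set d = 5 in both groups and q(PACT) = 20%. With q(control) = 20%, the bias is 1.0 − 1.0 = 0. With q(control) = 30%, it is 1.0 − 1.5 = −0.5, against PACT. The assumption in step 4 decides the answer, so its figures show scale only. The d that matters is also what remains after matching, baseline adjustment and propensity stratification.

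**The case against.** The strongest objection is that the Participants sentence gives a time of starting, not a condition. It does not say that refusing the study means going without the team, or that signing requires accepting it, and the consent form is not shown. Design describes a model that reaches everyone in the uptake area, and Status reports referrals to the team before enrolment. Both suggest that the service can run without trial consent. This stands. A reader might infer that people who refuse are denied PACT, or that decliners certainly leave the PACT group; the article does not establish either. What remains is that the sections leave the matter open, although membership of the analysis set depends on it.

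Three stronger readings are also tempting and not supported:

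- **Selection in one group only, in favour of PACT.** Controls self-select too, by accepting repeated questionnaires with no service in return. Only refusal of the team is confined to one group. The net bias could be near zero or run against PACT.
- **A contradiction between Design and Analyses.** Consent is itself an inclusion criterion, so the Design sentence is not literally false. It merely reads more broadly than the set analysed.
- **A difference that adjustment cannot touch.** Baseline Patient Activation Measure, socio-economic status and previous health care experiences are collected, and the list of propensity variables is open. They could remove part of the difference, but only what they capture.

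It is also fair that someone who signs and then does not use the team already stays in the PACT group. The gap concerns those who do not sign because of the team. Finally, the Discussion names lack of randomisation as the main limitation, and some consent-related selection comes with that. Tying the signature to different offers is an addition that could be avoided without randomising.

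**Conclusion.** The point holds in a limited form. The intention-to-treat set is built from signatures that, as written, go with service plus study in one group and study alone in the other. This allows differential selection on willingness to have the team, which cannot be observed in controls and is adjustable only through measured proxies.

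Its direction and size are unknown. The illustrative 0.3 to 3.2 points rests wholly on assumed refusal shares and assumed differences in change, and on no offsetting selection among controls. It shows that the bias could be anything from negligible to a large part of the 4-point target, not that it is. Whether the problem arises at all depends on whether receiving PACT is tied to study consent, which the article does not settle. The change is worth making because it alters who is analysed and is inexpensive.

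**What to change.** 1. Reconcile Design and Participants, in the light of Status, on whether receiving PACT depends on signing the study consent.
2. Use the same consent, covering data collection, at all four hospitals, and do not make it conditional on accepting the team.
3. Record acceptance of PACT separately at the intervention hospitals.
4. Keep patients who consent to data collection but decline the team in the intervention group for the intention-to-treat analysis.

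The cost is a revised consent form and an ethics notification. The estimated effect will be slightly diluted, because some patients in the intervention group will not take up the team. Selection through willingness to answer questionnaires remains in both groups, but the decision to sign then concerns the same request everywhere.
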